### Study Design

The EPICC project includes 2 distinct aims. Aim 1 includes provider training. Providers will be trained on the use of education tools adapted in the formative work and the process of screening, counseling, initiation, and follow-up with clients interested in or already taking PrEP through our PrEP training modules and will complete TMI training. The effectiveness of the training will be measured quantitatively. Aim 2 is a longitudinal cohort study designed to test the newly adapted education tools through a hybrid type 2 effectiveness implementation cohort to assess PrEP uptake and adherence to PrEP among YMSM and provider provision of PrEP and competence with education tools to increase PrEP services. Aim 2 will include a mixed methods analysis. Figure 1 provides an overview of the EPICC project’s design. Formative work can be found elsewhere [17].

The mChoice project includes 3 aims. Aim 1 of the mChoice project is to conduct a hybrid type 2 trial testing the effectiveness of the mChoice clinical intervention to increase PrEP adherence and persistence among YMSM using PrEP. Aim 2 is to conduct in-depth interviews to assess multilevel factors at the patient level associated with selection of a PrEP regimen and switching patterns. Aim 3 is to provide training to health care providers to improve knowledge of PrEP clinical recommendations and enhance provider communication. Figure 2 provides an overview of the mChoice project design. Formative work findings can be found elsewhere [18].

**Figure 1 figure1:**

EPICC project design. EPICC: Expanding Pre-Exposure Prophylaxis (PrEP) in Communities of Color; YMSM: young men who have sex with men.

**Figure 2 figure2:**
[figure not shown]
mChoice project design.

### Data Collection

Every 6 months, study sites (EPICC and mChoice) will complete a clinic assessment that will include information around PrEP prescriptions issued, clinic services, financial assistance, and PrEP support services. This information will be collected prior to the provider training and will continue for the duration of the study to assess implementation efficacy. There will be a clinic assessment baseline and final, which is completed at the beginning of data collection and at the end and a shorter clinic assessment every 6 months. These assessments will capture data on clinic demographics, PrEP uptake and follow-up and provision of HIV and PrEP education.

The EPICC project’s aim 1 provider training consists of the completion of surveys prior to and after training components. Providers are rated on their use of TMI during standard patient interactions immediately after training and three months post training. Aim 2 data collection will occur using surveys every three months, project app paradata, and exit interviews. Additionally, we will conduct focus group discussions with providers at the end of the longitudinal cohort.

The mChoice project’s aim 1 data collection will occur using surveys every three months, and project app paradata. Aim 2 data collection will occur using in-depth interviews with a subsample from aim 1. The mChoice project’s aim 3 provider training consists of the completion of surveys prior to and after training components and an interview following completion of the training.

### Provider Training

Each project will enroll participants for both provider training and the cohort from unique study sites. Figure 3 includes a map of each project’s enrollment sites.

The EPICC project team developed online PrEP training modules to educate providers on currently available PrEP options and how to engage clients in open discussions around sexual health and PrEP options. The goal of these open discussions between providers and clients is to encourage shared decision-making on PrEP options. The flexible and interactive modules were created using the Easygenerator online authoring tool, which allows learners to complete their assigned courses over multiple sessions at any time. The interactive features used throughout the modules are designed to keep providers engaged. Some of these features include checks for understanding, embedded videos, and links to external content. Each module also contains at least 1 case-based scenario. These scenarios are based on real-world interactions that study team providers experience during interactions with clients.

The EPICC project team developed these modules using a variety of content sources, including CDC-produced guidelines and materials, research papers, and expert guidance. In addition to modules covering PrEP regimens, we also included modules on the need for PrEP, PrEP screening and startup, postexposure prophylaxis (PEP), and PrEP adherence and persistence. The modules were refined to their final form through an iterative feedback process with subject matter experts within the EPICC project team. Both EPICC and mChoice project teams will use these modules in their respective provider training. Table 1 lists the titles and brief descriptions of each module.

Figure 4 includes screenshots of content within the modules that highlight interactive elements used throughout the course. The video image shown is from “Let’s Talk About Sexual Health” [19] produced by the CDC and BeSmartBeWell.com.

In the EPICC project, after completing the online PrEP training modules, providers will attend live, online TMI training sessions led by a member of the motivational interviewing (MI) network of trainers. The training has been split into distinct training modules: (1) introduction to TMI and PrEP choice; (2) TMI spirit, cultural humility, antiracism, and stigma reduction; (3) managing counter change talk and discord with empathy and autonomy support; and (4) eliciting and motivation for PrEP. There will be 2 training sessions lasting approximately 3 hours conducted virtually over 2 days. The training uses videos of PrEP providers demonstrating TMI integrated with antiracism and cultural humility that were created specifically for this study. The workshops are structured with cooperative learning activities, video examples, and behavioral skill acquisition steps (modeling, verbal and behavioral rehearsal, feedback). After the live, online training is completed, providers will complete a 15-minute standard patient interaction assessment, where a member of the study team will act as a client and the provider will attempt to use TMI techniques during their interaction. The conversation will be coded by a study team member using the MI Coach Rating Scale [20], and a feedback report will be generated and sent to the provider. The report will include strengths and areas for improvement, with video links featuring skills identified as areas for improvement. Three months after completing the TMI training sessions, providers will complete an additional standard patient interaction assessment with the same feedback format. Providers will also complete a brief survey prior to starting the online modules, which will include demographics; PrEP familiarity and attitudes; and PrEP use and future intentions. Providers will complete another survey after the TMI training sessions are over, which will include similar questions to the first survey to assess for change after completing online modules and TMI training.

After completing the online PrEP training modules, providers in the mChoice project will watch a 10-minute video on cultural competency and humility in PrEP care training developed specifically for this study. This module consists of an introduction to cultural competency and humility and exemplifies how these concepts are key components to PrEP care. Like the EPICC project team, sources for the video include information from CDC guidelines, CDC-produced materials, and peer-reviewed journal–cited research papers. For example, the CDC’s 5Ps approach to gathering sexual history is highlighted as a critical step in the context of PrEP care. More information about the 5Ps approach can be found on the CDC’s website [21]. Useful tips, such as using layperson’s terms that are also anatomically correct, making eye contact, and not appearing to be in a hurry, are mentioned throughout. Simultaneously, this module emphasizes the importance of making clients feel comfortable and respected and allowing the client to guide the conversation. This module aims to inform providers about how to best interact with clients and demonstrate racial and ethnic diversity among clients through the use of dynamic graphics. The module also provides training to facilitate provider-client communication so that there can be effective shared decision-making. It will be included in the PrEP Choice provider series launched through Easygenerator.

**Figure 3 figure3:**
[figure not shown]
Map of EPICC and mChoice project enrollment sites. EPICC: Expanding Pre-Exposure Prophylaxis (PrEP) in Communities of Color.

**Table 1 table1:** Online PrEP^a^ training module titles and topics used in EPICC^b^ and mChoice Studies.

Module title	Topics covered
Module 1: Why Do We Need PrEP?	HIV epidemic in the United States, the EHE plan, PrEP update in the United States, and PrEP efficacy and effectiveness
Module 2: Who and Why for PrEP	PrEP guideline changes, PrEP screening, and HIV testing recommendations
Module 3: What Is PEP and Who Should Get It?	PEP screening, prescribing, and monitoring
Module 4: Considerations in Choosing Among Oral PrEP Options	Oral PrEP regimens, oral PrEP initiation and follow-up, 2-1-1 or on-demand PrEP, and oral PrEP side effects
Module 5: Considerations in Prescribing and Monitoring Injectable PrEP	Injectable PrEP initiation, follow-up, adherence, side effects, and future PrEP modalities
Module 6: Maximizing PrEP Adherence and Persistence	Adherence counseling components, PrEP implementation, and cost considerations

^a^PrEP: pre-exposure prophylaxis.

^b^EPICC: Expanding PrEP in Communities of Color.

**Figure 4 figure4:**
[figure not shown]
Screenshots and descriptions of interactive content within online PrEP modules used in EPICC and mChoice provider training.

### Longitudinal Cohort

Both EPICC and mChoice projects will enroll a cohort of 400 participants. Study participation will range from 12-18 months, depending on the study enrollment date. Eligibility criteria include (1) age 18-39 years, (2) the male sex, (3) ever had sex (as a top or a bottom, insertive or receptive) with a person who has a penis, (4) have an active prescription for PrEP (including both new prescriptions at baseline or refills), (5) receive care at 1 of the participating study sites, (6) provide a mailing address within the 50 states where packages can be received, (7) have daily smartphone access, and (8) be fluent in written and spoken English or Spanish. Cohort participants will be recruited by the clinic staff during scheduled visits, through study advertisements placed in clinic waiting rooms, or through study advertisements on social media platforms.

Each project team builds off prior work to adapt their unique digital health tools poised to support PrEP choice and ongoing adherence. The EPICC project builds from the HealthMpowerment (HMP) intervention. HMP is a theory-based status app designed to provide health and wellness information and resources relevant to young people via a mobile optimized platform. HMP was created based on the Integrated Behavioral Model [22-24]. HMP is flexible and easy to adapt for specific populations and health topics. The EPICC project’s version of HMP includes resources most relevant for our study population. The mChoice app was created based on the Information System Research framework and builds on formative work to develop a PrEP adherence and monitoring app [25-27]. The mChoice app was built in collaboration with Compliance Meds Technologies (CMT) CleverCap. CMT is an mHealth technology solutions provider that develops adaptable technology to promote health. The CleverCap app is linked to a CleverCap device, which is an electronic pill bottle that records when the cap opens and closes and tracks medication adherence. The CleverCap app was customized to the needs of the mChoice project to support PrEP adherence among YMSM. It offers PrEP resources, such as 2 client-facing PrEP training modules created by the study team and a sexual activity log. It can be programmed for the use of participants who are taking any of the 3 PrEP regimens: oral (daily or event driven) or injectable. Table 2 lists the features of each project’s mobile app.

**Table 2 table2:** Description of EPICC^a^ and mChoice digital health support tools.

Feature	EPICC	mChoice
Resources	Educational content across a range of health topics, as well as support for app engagement and behavior change through information and skill building	Participant-facing PrEP training modules, links to the CDC^b^ website
Adherence support	Medication tracker to support oral, injectable, or event-driven PrEP adherence	Electronic adherence monitoring through the use of the CleverCap app and device
Sexual behavior tracking	Sexual activity log	Sexual activity log
Connection to care	“Ask the Expert” feature to allow providers to anonymously answer user questions and connect users to resources	Chat function to communicate with the study team
Engagement features	Gamification with badges and avatars earned for completing activities	Adherence statistics for participants taking oral daily PrEP
Integrations with test kits	Yes	N/A^c^

^a^EPICC: Expanding Pre-Exposure Prophylaxis (PrEP) in Communities of Color.

^b^CDC: Centers for Disease Control and Prevention.

^c^N/A: not applicable.

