## Methods

### Ethical Considerations

This works follows a protocol reviewed and accepted by the Institutional Review Boards of Florida State University (approval number 00003623) and Columbia University (approval number AAAT8812). Participants will provide informed consent prior to beginning any study activities. The consent form includes standard consent sections describing the purpose of the study, the procedures to be followed, and the risks and benefits of participation. The consent form went through multiple reviews by team members to ensure the language was sufficiently simple. A certificate of confidentiality was obtained from the CDC. All data and records will be stored on password-protected servers. No identifiable data will be published.

EPICC project providers will be compensated US $50 for completing the pretraining survey; US $50 for completing online PrEP training modules, tailored motivational interviewing (TMI) training sessions, the posttraining survey, and the first standard patient interaction; and US $50 for the 3-month posttraining standard patient interaction. Cohort participants will be compensated US $50 for the baseline survey and app download, US $50 for an optional onboarding visit, US $25 for the 3-month follow-up survey, US $50 for the 6-month follow-up survey, US $25 for the 9-month follow-up survey, US $50 for the 12-month follow-up survey, US $25 for the 15-month follow-up survey, and US $50 for the 18-month follow-up survey. For home-based dried blood spot (DBS) collection, cohort participants will be compensated US $50 for the baseline, 6-month, and 12-month collections and US $75 for the 18-month collection. A US $50 bonus will be provided to participants who complete the first 3 collections. Participants who complete the exit interviews will be compensated US $50. Providers who complete focus group discussions will be compensated US $75.

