### Primary Outcome Measures

The primary outcome for provider training is PrEP familiarity, PrEP beliefs, and intentions to use PrEP measured at pre- and posttraining. The primary outcome for the cohort is PrEP adherence. For the EPICC project, adherence outcomes will be measured by using blood and will be tailored for oral PrEP modality (daily or 2-1-1) and categorized as protective (1) or not protective (0). The protective level of PrEP in the blood is defined as ≥4 doses taken per week, and the not-protective level is defined as <4 doses taken per week. Adherence outcomes for participants on CAB-LA will be determined by the timely administration of injections. The timely administration of the second injection is defined as within +/–1 week of the target date and within +/–2 weeks of the target date for subsequent injections. For the mChoice project, adherence outcomes, as measured by using urine, will be assessed by testing TFV and FTC levels in urine specimens collected from participants who report daily use of PrEP containing TFV and FTC. The mChoice project will also measure adherence by electronic medication monitoring via the CleverCap device, EHR data, and self-report.

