#### The EPICC Project

##### Sample Size and Power Calculations

The sample size for this study was determined based on feasibility after considering the intended analyses and multiple parameter estimates. With 400 participants, the minimum detectable difference in the PrEP adherence and persistence rates was 5.6%, assuming 15% loss to follow-up and a reference rate of 20%, at 0.80 power with a 1-sided test and 0.05 type I error. For baseline to postintervention analyses, simulation-based results indicated the minimum detectable difference from a baseline rate of 20% was approximately 9% (odds ratio 1.6), assuming again 15% loss to follow-up, at 0.80 power with a 1-sided test and 0.05 type I error [39].

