##### Analysis Plan

Baseline participant characteristics will be described for the entire sample and disaggregated by regimen, site/region, ethnicity, level of HIV risk perception, substance use, PrEP experience (naive vs familiar), partner relationship status, and the other variables of interest included in Table S1 in Multimedia Appendix 1.

To determine any differences in discontinuation and nonadherence, we will use Cox proportional hazards to analyze (1) time to first discontinuation and (2) time to first nonadherence by regimen using PrEP adherence measures. To incorporate observations after the first discontinuation or after the first nonadherence, including allowing for the possibility of restarting on PrEP after discontinuation and for periods of nonadherence followed by a period of adherence, we will use a multilevel survival model by including a frailty term in the model to allow analysis of recurrent events [40]. We will follow the same analytic strategy for other dichotomous primary and secondary effectiveness and implementation outcomes. For the composite measure of number of prescriptions (primary implementation outcome), we will fit a multilevel linear or a generalized linear regression model, again using all the time point data available to assess the strength of the associations between the composite measure for the number of prescriptions and the predictor variables. To examine the trajectories of regimens, we will use generalized linear mixed models (GLMMs) and a survival model to assess the time to each regimen switch.

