##### Primary Outcome

A GLMM, also called an individual growth model and a multilevel model, with an appropriate link function will be used to compare the pre- and postintervention difference for each outcome. The GLMM allows different trajectories for each participant, and this method is appropriate to compare outcome changes after the implementation of the intervention, with the control of baseline values. Analyses will be conducted for the full sample and by study location (New York City and Birmingham) separately [44].

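### The pre-post adherence contrast pools new PrEP starters with established users, so starting PrEP can look like improvement (EPICC) or change who is compared (mChoice)

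*Protocol article*

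**What the plan says.** **Who is enrolled.** The eligibility list under Longitudinal Cohort requires that participants "have an active prescription for PrEP (including both new prescriptions at baseline or refills". It sets no cap on the share of new prescriptions and no stratification. Each project plans 400 participants.

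**EPICC.**
- A blood spot is collected at entry: "For home-based dried blood spot (DBS) collection, cohort participants will be compensated US $50 for the baseline, 6-month, and 12-month collections" (Ethical Considerations).
- The primary adherence outcome is binary for oral regimens: "The protective level of PrEP in the blood is defined as ≥4 doses taken per week", and anything lower is not protective (Primary Outcome Measures).
- The power section sizes a contrast with baseline: "For baseline to postintervention analyses, simulation-based results indicated the minimum detectable difference from a baseline rate of 20% was approximately 9" percentage points, an odds ratio of 1.6.
- The Analysis Plan lists "PrEP experience (naive vs familiar" among the variables by which baseline characteristics are broken down. It gives the variable no role in a pre-post comparison.

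**mChoice.**
- The primary analysis is a single-group mixed model that "will be used to compare the pre- and postintervention difference for each outcome". The only adjustment named is "with the control of baseline values".
- Urine adherence is assessed in "specimens collected from participants who report daily use of PrEP containing TFV and FTC" (Primary Outcome Measures). Cohort Procedures likewise restricts sampling to people reporting use.

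**Design.** The Limitations section accepts that this is a cohort study without randomisation.

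**The concern.** In a single-group pre-post design, the baseline value is the only stand-in for what would have happened without the intervention. It serves that purpose only if it measures the same thing before and after. For someone who has just been handed a first prescription, a baseline drug level does not measure adherence, because there has been nothing to adhere to.

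The two projects meet this problem differently. EPICC takes a baseline blood sample and scores it 0 or 1, so a starter sampled before, or soon after, the first dose scores 0 and can only stay level or rise. In mChoice, a person who has not begun gives no urine result, so the pre values come from established users and the post values from established users plus starters. Controlling for baseline values solves neither problem: the baseline is itself the artefact in one project and absent in the other, and there is no comparison group to absorb the shift.

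At stake is whether a positive adherence result can be told apart from people simply beginning treatment.

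**Working it through.** **1. The plan's own figures.** EPICC's 5.6 points is reproduced by a one-sample proportion test: n = 400 × 0.85 = 340, null 20%, 1-sided 0.05, power 0.80, giving 5.56 points. For the pre-post figure, 20% to 29% is an odds ratio of (0.29/0.71)/(0.20/0.80) = 1.63, matching the stated 1.6. The 9 points came from a simulation whose within-person correlation is not given, so it can only be approximated. A two-proportion formula at n = 340, 1-sided, gives 8.1 points, and power of 0.86 for 9 points.

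**2. Artefact when a starter scores 0 (EPICC blood outcome).** Let s be the share of starters with a baseline of 0, and a the adherence rate. Assume no intervention effect: established users adhere at rate a at both times, and starters go from 0 to a. Then

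- pre = (1 − s)a, post = a, apparent gain = s × a;
- spurious odds ratio = [a/(1 − a)] / [pre/(1 − pre)].

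Example: a = 0.60, s = 0.30 gives pre = 0.42, and 1.5/0.724 = 2.07. Neither s nor a is in the article, so a range is shown.

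| a | s = 5% | s = 10% | s = 20% | s = 30% | s giving 9 points | s giving OR 1.7 |
|---|---|---|---|---|---|---|
| 20% | 1.07 | 1.14 | 1.31 | 1.54 | 45% | 36% |
| 40% | 1.09 | 1.19 | 1.42 | 1.71 | 22.5% | 30% |
| 60% | 1.13 | 1.28 | 1.62 | 2.07 | 15% | 22% |
| 80% | 1.26 | 1.56 | 2.25 | 3.14 | 11% | 12% |

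EPICC's planned 20% to 29% would arise with no effect if a = 29% and s = 1 − 0.20/0.29 = 31%.

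**3. Effect on the test.** This uses a McNemar approximation with n = 340, 1-sided 0.05, a = 60% and an assumed correlation of 0.45 among established users (the middle of mChoice's 0.3 to 0.6). The chance of a false positive is about 0.27 at s = 5%, 0.65 at 10% and 0.91 at 15%, against a nominal 0.05.

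**4. mChoice urine outcome.** Here a starter who has not begun is missing, not 0, so the table does not apply. In raw proportions, with established users at a_e and starters at a_n, pre = a_e and post = (1 − s)a_e + s·a_n. The shift with no effect is s(a_n − a_e), which can go either way and vanishes if the groups adhere equally. A mixed model leans partly on within-person change, which dampens but does not necessarily remove the shift. The baseline sample also shrinks: if s = 30%, 400 × 0.70 = 280 have a baseline, and after 20% attrition 280 × 0.80 = 224 pairs remain instead of 400 × 0.80 = 320.

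**5. Cost of using established users only.** The detectable effect scales by roughly 1/√(1 − s). At s = 30% this is 1/√0.70 = 1.195. EPICC: 9 × 1.195 = 10.8 points. mChoice: exp(1.195 × ln 1.7) = 1.89. As a check with the two-proportion formula, EPICC at n = 340 × 0.70 = 238 goes from 8.1 to 9.8 points, and power for 20% to 29% falls from 0.86 to 0.74.

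**The case against.** Several points on the other side stand.

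- **EPICC's written analysis is not a pre-post model.** Its Analysis Plan specifies Cox models for first discontinuation and first nonadherence, frailty models for recurrent events, and models for regimen trajectories. The baseline contrast appears only in the power section. In a time-to-nonadherence model, a starter's low first value would, if scored at all, count against adherence.
- **mChoice starters are not scored 0 on urine.** A reader might infer that starting PrEP is counted directly as the mChoice effect. For urine, the article does not support that: only people reporting use are tested. How the electronic cap, health record and self-report measures code someone who has not begun is not stated.
- **A new prescription is not the same as a first use.** Restarts and regimen changes may qualify with drug already on board, and the timing of EPICC's home collection relative to the first dose is not given.
- **Other outcomes escape.** Long-acting injectable users are judged on injection timing, not drug level. Persistence is not inflated this way, since everyone holds an active prescription at entry.
- **The size is conditional.** At 60% adherence, 5% starters give an odds ratio of only 1.13.

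It can also be said that covariates and baseline coding belong in an analysis plan that is not shown. That is only partly persuasive. The article does fix the mixed population, the binary coding, the baseline sample and mChoice's pre-post model with its one named adjustment, and these together create the problem.

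**Conclusion.** The concern holds in a limited form. The cohort mixes people beginning PrEP with people already taking it, and as written the pre-post adherence contrast does not separate them. In EPICC, this turns initiation into apparent improvement for oral first-time starters sampled before or soon after the first dose, in whatever baseline-to-postintervention analysis the power section refers to. In mChoice, it makes the before and after groups differ in composition and leaves fewer than 400 baseline values; the direction of any resulting bias is not fixed.

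The size rests on two assumed quantities. At 60% adherence and 0-scoring, the spurious odds ratio runs from 1.13 (5% starters) through 1.28 (10%) and 1.7 (22%) to 2.07 (30%). The share might be small enough for the bias to matter little.

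A reader might conclude that both projects are bound to report a false effect. The article does not support that: the starter share is unknown, and EPICC's survival analyses, persistence and injection timeliness lie outside the mechanism. This should be fixed before analysis, but it does not invalidate the study.

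**What to change.** In any pre-post adherence analysis, in either project:

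1. Add an indicator for new versus established user and its interaction with time, or stratify on it. Define it by actual prior use, so that restarts and switches are classed deliberately. Both projects already collect prescription data from health records, and EPICC also records PrEP experience.
2. Take the pre-post effect from established users. Report starters separately, from their first on-treatment measurement.
3. State for EPICC whether the baseline-to-postintervention contrast will be analysed, and for mChoice how people without a baseline urine result enter the model.
4. Restate the detectable effect for the established-user subset.

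Starters stay in the study and in its reporting, which matters because the aims cover people beginning PrEP as well as those continuing it. Excluding them altogether would be harder to defend.

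The change is to analysis wording, with no new visits or samples. Its price is precision: if 30% are starters (an assumed share), EPICC's 9 points becomes about 10.8 and mChoice's odds ratio of 1.7 about 1.9, both approximate. The headline effect would also describe established users only, since starters have no usable pre-intervention adherence value.
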